## Abstract

**Background:**

Tenofovir disoproxil fumarate (TDF) is key component of pre-exposure prophylaxis (PrEP) and antiretroviral therapy (ART) for HIV, but existing tools to monitor drug adherence are often inaccurate. Detection of tenofovir (TFV) in accessible biological samples, such as fingerprick blood, urine or oral fluid samples could be a novel objective measure of recent TDF adherence. To measure TFV concentrations associated with different levels of TDF adherence, we designed a randomized clinical trial to assess the blood, urine and oral fluid concentrations of TFV in adults with perfect, moderate and low drug adherence.

**Methods/design:**

A randomized, open-label, clinical pharmacokinetic study of tenofovir in healthy adult volunteers without HIV or Hepatitis B infection in Thailand. Consenting, eligible participants are randomized (1:1:1) among three groups to receive a controlled number of TDF (300 mg) doses in a combination pill with emtricitabine (FTC, 200 mg) for six weeks. Participants in **Group 1** receive a single TDF/FTC tablet once daily (Perfect adherence); **Group 2** receive a single TDF/FTC tablet 4 times/week (Moderate adherence); and **Group 3** receive a single TDF/FTC tablet 2 times/week (Low adherence). Blood, plasma, urine and oral fluid samples are collected for drug measurement during three study phases: (i) initial 6-week treatment phase; (ii) intensive 24-h blood sampling phase after 6 weeks; (iii) 4-week washout phase. Thirty adults with evaluable pharmacokinetic samples (10 per group) will be enrolled [based on ensuring 25% precision in pharmacokinetic parameter estimates]. Pre-dose drug concentrations during the treatment phase will be descriptive and comparisons between groups performed using a Kruskal-Wallis test. A non-compartmental pharmacokinetic analysis will be performed on the intensive sampling data at Week 7 and the time course of TFV washout in the difference biological matrices will be reported based on the detected concentrations following drug cessation.

**Discussion:**

The results of this randomized trial will define the target concentration thresholds of TFV in blood, urine and oral fluid that can distinguish between different levels of TDF adherence. Such adherence ‘benchmarks’ can be applied to real-time drug testing and novel point-of-care tests to identify individuals with poor PrEP or ART adherence.

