### Statistical analysis

The primary endpoints are descriptive pharmacokinetics endpoints. A Kruskal-Wallis test will be used to compare basic demographic variables between the three groups. A non-compartmental pharmacokinetic analysis will be performed on the TFV concentration data generated from the intensive blood samplings at Week 7. Pharmacokinetic parameters in plasma and blood (venous and fingerstick) will include: area-under-the-curve (AUCτ), maximum concentration (C_max_), time to C_max_ (T_max_), apparent clearance (CL/F), apparent volume of distribution (V/F), and minimum concentration (C_min_). AUCτ will be determined using the linear trapezoidal method. C_max_, C_min_ and T_max_ will be taken directly from the observed concentration-time data. The terminal slope (λz) will be determined from the log-linear portion of the curve, and the half-life will be calculated as Log_10_ (2)/λz. Total body clearance (CL/F) will be calculated using Dose/AUC_0-τ_. The fraction of TFV excreted unchanged in the urine (Fe_TFV_) will be determined as the total amount of TFV excreted during the urine collection period following cessation of RDF divided by the dose. The renal TFV clearance (CLR) will be calculated by multiplying Fe_TFV_ and CL/F. We will calculate median (range), means (standard deviations), and geometric means with 95% confidence intervals for each PK parameter.

We will compare pre-dose TFV concentrations in specimens collected during the treatment lead-in period (i.e. before 2nd dose of TDF/FTC, and at Weeks 3, 5 and 7) using a Kruskal-Wallis test. We will report the time course of TFV washout in blood, plasma, urine and oral fluid based on the detected drug concentrations following drug cessation. We will perform non-pharmacokinetic statistical analyses using Stata (Version 10.0, StataCorp LP, Texas, USA).

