## Discussion

The efficacy to TFV-based PrEP and ART are highly dependent on adequate medication adherence to maintain sufficient drug concentrations. Improvements in real-time drug testing and novel point-of-care tools are needed to help improve monitoring of drug adherence. Detecting TFV concentrations in easily accessible biological specimens, such as fingerprick blood, urine or oral fluid, may act as a simple objective measure of recent TDF adherence. The objective of this trial is to characterize the pharmacokinetics of TFV among healthy volunteers with controlled drug adherence (perfect, moderate, and low) in fingerprick blood, urine and oral fluid. The information generated from this clinical study will be critical to determine if TFV concentrations in these biological specimens can distinguish between different levels of TDF adherence.

Moreover, these data are highly relevant to research towards the development of inexpensive, rapid, point-of-care drug measurement tests for monitoring medication adherence. The clinical data on the pharmacokinetics of TFV (and/or FTC) in these biological specimens with respect to controlled adherence will help define the target thresholds, or adherence ‘benchmarks’, that can facilitate clinical interpretation of real-time testing and novel point-of-care tests. The introduction of scalable TFV-based point-of-care tests may allow rapid identification of people struggling with PrEP or ART adherence, in order to develop and implement targeted adherence interventions. Improving adherence to both PrEP and ART will help reduce and prevent HIV transmission, while also preserving the use an important drug in the efforts to end the HIV/AIDS epidemic.

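### The only named between-group test, an omnibus Kruskal-Wallis on pre-dose tenofovir, is near certain to reject and cannot show that adjacent adherence levels can be told apart, which the abstract says the trial will establish.

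*Protocol article*

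**What the plan says.** Three parts of the protocol article bear on this.

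- **The claim.** The Discussion paragraph of the abstract says that the results "will define the target concentration thresholds of TFV in blood, urine and oral fluid that can distinguish between different levels of TDF adherence". The main Discussion is more cautious: the information "will be critical to determine if TFV concentrations in these biological specimens can distinguish between different levels of TDF adherence", and the data "will help define the target thresholds, or adherence" benchmarks.
- **The comparison.** The Methods/design paragraph of the abstract says: "Pre-dose drug concentrations during the treatment phase will be descriptive and comparisons between groups performed using a Kruskal-Wallis test". The Statistical analysis section repeats this: "We will compare pre-dose TFV concentrations in specimens collected during the treatment lead-in period", namely before the second dose "and at Weeks 3, 5 and 7) using a Kruskal-Wallis test". No other between-group comparison of concentrations is named.
- **The status of the analysis.** The same section says: "The primary endpoints are descriptive pharmacokinetics endpoints". The Sample size calculation section sets 10 per group from the precision of the mean plasma AUC, not from any test or cut-off.

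**The concern.** Kruskal-Wallis asks whether the three groups share one distribution. The abstract's claim is about something else: whether a concentration measured in one person can place that person at one adherence level rather than the next.

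A small omnibus p-value can come entirely from the group on 2 tablets a week. It does not say whether daily dosing separates from 4 times a week, which is probably the harder contrast in practice. It also measures no overlap between groups.

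If the test is almost bound to reject, its result adds nothing. A reader who sees a significant result beside the abstract's promise could then take the thresholds as established for every step of the adherence scale.

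**Working it through.** **1. The article's own figure.** Sample size calculation gives SD 1.37 and half-width 0.83 μg·h/mL at 90% confidence. The condition is t(0.95, n−1) × 1.37/√n ≤ 0.83. For n = 9 the left side is 0.849; for n = 10 it is 0.794. Ten per group reproduces. It is a precision target for a group mean, not for classifying individuals.

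**2. Sampling times.** Table 1 doses Group 2 on Monday, Wednesday, Friday and Saturday, and Group 3 on Monday and Thursday. Week 3, 5 and 7 pre-dose samples are taken on Monday mornings. With morning dosing, the last tablet was 24 h (Group 1), 48 h (Group 2) or 96 h (Group 3) earlier.

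**3. Expected plasma troughs.** The Background gives a 17 h half-life, so k = ln 2/17 = 0.0408 per hour. Assuming one-compartment decay, sum exp(−k × hours since dose) over past doses:

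- Group 1: 0.376/(1 − 0.376) = 0.602
- Group 2: 0.141 (48 h) + 0.053 (72 h) + 0.0075 (120 h) + 0.001 (168 h) = 0.203
- Group 3: 0.020 (96 h) + 0.001 (168 h) = 0.021

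The ratios are 1 : 0.34 : 0.035. Group 1 is 2.96 times Group 2, and Group 2 is 9.66 times Group 3.

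**4. Spread.** The AUC CV is 1.37/3.32 = 0.413, so log SD = √ln(1 + 0.413²) = 0.40. Using this for troughs is an assumption. The article gives no variability for urine or oral fluid, so 0.8 and 1.2 are also shown.

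**5. Omnibus result against pairwise separation.** Log-normal data, 10 per group, two-sided 0.05, 4,000 runs. ROC area = Φ(ln(ratio)/(SD × √2)).

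| Log SD | Kruskal-Wallis rejects | Kruskal-Wallis rejects if Groups 1 and 2 are identical and Group 3 is 9.66-fold lower | Rank test, 1 vs 2, rejects | ROC area, 1 vs 2 | ROC area, 2 vs 3 |
|---|---|---|---|---|---|
| 0.40 | 100% | 100% | about 100% | 0.97 | >0.99 |
| 0.8 | 100% | 100% | 77% | 0.83 | 0.98 |
| 1.2 | about 100% | 98% | 43–44% | 0.74 | 0.91 |

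The omnibus column hardly moves while the ROC area for Group 1 vs 2 falls from 0.97 to 0.74. The test also rejects when there is no difference between Groups 1 and 2 to find.

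**6. Precision of any cut-off.** Exact (Clopper-Pearson) 95% intervals for the proportion of one group of 10 classified correctly:

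- 10/10: 69% to 100% (lower limit 0.025^(1/10) = 0.692)
- 9/10: 55% to 99.7%
- 8/10: 44% to 97%

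**The case against.** The strongest reply is that the article never offers Kruskal-Wallis as the route to thresholds. The primary endpoints are descriptive, and group-wise concentrations and the washout course can feed a later threshold analysis. A cut-off method may be in the full protocol or analysis plan, neither of which is shown. This stands: the absence of a cut-off method from an article is not an error, and it is not the point made here. What remains is that the abstract states as assured what the main Discussion leaves open, and that the one comparison the article does name cannot bear on it.

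Three stronger readings are tempting, and the documents do not support them.

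- **That ignoring the order of the groups costs important power.** At the planned Monday troughs it does not in plasma. Kruskal-Wallis and the Jonckheere-Terpstra trend test both reject in about 100% of runs up to log SD 1.2. Nor would a trend test cure the problem: when only Group 3 differs, by 1.5 SD, it rejects in about 83% of runs against 89% for Kruskal-Wallis. A loss in urine or oral fluid is possible, but the article gives no variability from which to size it.
- **That values from four visits will be pooled as if independent.** The Statistical analysis section lists the visits without saying so, and the abstract speaks of comparisons in the plural. One test per visit is the natural reading.
- **That the levels cannot be separated.** On the article's own plasma CV, Groups 1 and 2 separate well at the Monday trough (ROC area 0.97).

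**Conclusion.** The point holds as a mismatch between the abstract's claim and the named comparison. On the stated half-life and dosing days, the omnibus test is near certain to reject, and rejection does not show that daily dosing can be told from 4 times a week, or 4 from 2. At log SD 1.2 it rejects in about 100% of trials, while a direct test of Group 1 against Group 2 has only 43% to 44% power.

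The figures assume one-compartment decay, morning dosing, log-normal concentrations and, for 0.40, that the AUC CV applies to troughs. The values 0.8 and 1.2 are a range, not estimates from the documents. The 17 h half-life is for plasma, so the ratios need not carry over to other matrices.

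The Kruskal-Wallis test is valid for the question it asks, and the sample size reproduces for its stated aim. The point concerns reporting and wording, not the design.

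**What to change.** 1. In Statistical analysis, state that groups are compared at each visit, or on one steady-state value per participant (for example the mean of the log Week 3, 5 and 7 values).
2. For each matrix, report the three pairwise contrasts (1 vs 2, 2 vs 3, 1 vs 3) as ROC areas with confidence intervals. Kruskal-Wallis may stay as a preliminary test; an ordered trend test is optional.
3. Report any cut-off with cross-validated (for example leave-one-out) sensitivity and specificity and exact intervals. If the full protocol or analysis plan already sets this out, a pointer to it is enough.
4. Reword the abstract's Discussion to match the main text: the data will help define thresholds, or will give provisional ones.

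The cost is a little more analysis on data already being collected, with no added participants, samples or visits. The price is candour: at 10 per group the accuracy estimates will look imprecise, with a lower 95% limit of at most 69% for any single group.

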**Trial registration:**

ClinicalTrials.gov Identifier NCT03012607.

## Background

Daily oral tenofovir-based pre-exposure prophylaxis (PrEP) has been shown to be safe and effective in reducing the risk of HIV acquisition in adults [1–3]. Truvada®, composed of 300 mg of tenofovir disoproxil fumarate (TDF) and 200 mg of emtricitabine (FTC), is approved for PrEP by the US Food and Drug Administration [4] and is now recommended by the World Health Organization (WHO) for people at substantial risk of HIV infection as part of combination HIV prevention approaches [5]. TDF is also recommended by the WHO as part of first-line antiretroviral therapy (ART) and at the end of 2014 approximately 70% of people on first-line ART were taking a TDF-based regimen [6]. The efficacy of PrEP and ART, however, depend on adequate pill adherence to maintain sufficient drug concentrations [7]. Existing tools to monitor ART and PrEP adherence, such as patient self-reporting [8, 9], pill counting and home-based visits [9–11] have been shown to be ineffective. Electronic pill bottle caps/boxes are more accurate, but their high cost and complexity confine their utility to research settings. Real-time drug testing through simple, low-cost tools to identify poor PrEP or ART adherence would be valuable to help maintain the success of global HIV treatment and prevention programs.

TDF has favorable pharmacokinetic properties for an objective measure of drug adherence. TDF is a prodrug that is rapidly converted to tenofovir (TFV) after oral administration via esterase hydrolysis after absorption [12]. Once inside HIV-infected CD4 T cells, TFV is converted to its active form—TFV-diphosphate (TFV-DP) [12–14]. TFV has a plasma elimination half-life of 17 h and TFV-DP has an intracellular half-life in peripheral blood mononuclear cells (PBMCs) of 4.2 days [15]. An intracellular TFV-DP concentrations of >16 fmol/10^6^ PBMCs was associated with a 90% HIV risk reduction (EC_90_) in HIV acquisition and with ≥4 doses of TDF per week would yield TFV-DP concentrations in PBMCs associated with a 96% HIV risk reduction [7]. While the detection of TFV in plasma and TFV-DP in PBMCs have been proposed as objective measures of recent and cumulative drug adherence, respectively, the use of more accessible biological samples, such as fingerprick blood, urine, or oral fluid samples, would be preferable for real-time drug testing for adherence.

Tenofovir is detectable in whole blood [15, 16], urine [17], and oral fluid [18]. Our hypothesis is that the detection in TFV in a fingerprick blood, urine and/or oral fluid sample provides an indication of recent TDF adherence. However, to date no data are available on the concentration time-course of TFV in these biological matrices among adults with various degrees of TDF adherence. Such data are critical to establish the adherence ‘benchmarks’ for these matrices, which in turn can be applied to interpret drug level monitoring tests.

To address these issues, we have designed a randomized clinical trial to investigate the whole blood, urine and oral fluid pharmacokinetic of TFV in adults with perfect, moderate and low drug adherence. Plasma TFV and intracellular TFV-DP concentrations in PBMCs are also being evaluated to determine the degree to which they correlate with whole blood, urine and oral fluid TFV concentrations and to discriminate longer-term TDF adherence.

## Methods/design

The study is a randomized, open-label, pharmacokinetic study in healthy adult volunteers without HIV or Hepatitis B infection. The clinical study is being conducted in Sanpatong Hospital in Chiang Mai, Thailand, with the measurement of drug concentrations being performed at the Faculty of Associated Medical Sciences (AMS) at Chiang Mai University. All participants are screened for eligibility and asked to provide written informed consent before study participation.

Participant screening is performed within 14 days of enrollment. At screening, a detailed background demographic and health questionnaire is administered and blood is drawn for baseline assessments including complete blood count, HIV antibody testing, Hepatitis B surface Ag testing, renal and liver function tests. The results of the clinical examination and laboratory assessments are reviewed for the inclusion/exclusion criteria described below:

### Inclusion criteria

Willing/able to provided written informed consentAge ≥ 18 and <50 years oldHIV and Hepatitis B surface Ag negativeNormal renal function (estimated glomerular filtration rate (GFR) >60 mL/min by the Cockcroft-Gault equation)

### Exclusion criteria

Pregnant femaleAny significant lab abnormality of neutrophil count, hemoglobin, platelets, aspartate aminotransferase (AST), or alanine aminotransferase (ALT) (Defined as Grade ≥ 3 by Division of AIDS Table for Grading the Severity of Adult and Pediatric Adverse Events, Version 2.0, Nov. 2014)History of using PrEP or eligible to receive PrEPAny clinically significant diseases or clinically significant findings during the screening medical history or physical examination that, in the investigator’s opinion, might compromise participation in this studyAny concurrent participation in another clinical trial

### Randomization

At enrollment, eligible participants are randomized (1:1:1) among three groups to receive a controlled number of doses of TDF/FTC (300/200 mg) in a combination pill (Truvada®, Gilead Sciences), see Table 1. Participants in **Group 1** receive a single TDF/FTC tablet once daily for 6 weeks, representing ‘Perfect’ adherence (reference group). Participants in **Group 2** receive a single TDF/FTC tablet 4 times/week for 6 weeks, representing ‘Moderate’ adherence; and participants in **Group 3** receive a single TDF/FTC tablet 2 times/week for 6 weeks, representing ‘Low’ adherence. A total of 30 adults with evaluable pharmacokinetic (PK) samples (10 per group) will be enrolled.

**Table 1 Tab1:** Summary of the three randomization groups and the controlled levels of drug adherence

Randomized Groups	Level of Adherence	Controlled Intake of Truvada
Group 1 (*n* = 10)	‘Perfect’ Adherence (Daily)	Single tablet of Truvada® once daily for 6 weeks
Group 2 (*n* = 10)	‘Moderate’ Adherence (4 times/week)	Single tablet of Truvada® 4 times per week (Monday, Wednesday, Friday and Saturday) for 6 weeks
Group 3 (*n* = 10)	‘Poor’ Adherence (2 times/week)	Single tablet of Truvada® 2 times per week (Monday, Thursday) for 6 weeks

The 6-week treatment period was chosen in order to ensure concentrations of TFV in the different matrices, e.g. blood, plasma, urine, oral fluid, PBMCs, mimic the conditions expected in patients with chronic dosing. The 4-week washout period was based on the reported TFV half-life in the various biological samples under study. The study schema summarizing the treatment/washout periods and specimen sampling schedules are depicted in Fig. 1.

**Fig. 1 Fig1:**
[figure not shown]
Study schema

### Initial 6-week treatment phase

After randomization, all participants start Truvada® in the morning of the entry visit. During the next 6 weeks of controlled drug intake, pre-dose specimens are collected before the 2nd dose of TDF/FTC, and at Weeks 3 and 5 (both Monday morning, Table 2).

**Table 2 Tab2:** Summary of the clinical visits and laboratory testing for all 3 study groups

	Screening (≤14 days to Entry)	Entry	Prior 2nd Dose	Weeks 3 & 5	Week 7 (Monday/ Tuesday) PK visit	Weeks 7 (Wednesday Thursday, Friday, Saturday, & Sunday) Washout	Week 8 (Monday & Thursday) Washout	Week 9 Washout	Week 10 Start/End Washout
Informed Consent	x								
Physical Exam	x	x			x				
Medical History		x	x	x	x	x	x	x	x
Study Drug Dispensing		x	x	x	x				
Assess medication side effects			x	x	x	x	x	x	x
Adherence to Medication			x	x	x				
HIV Serology (2 ml)	x								
Hematology^a^ (2 mL)	x								
Chemistry^b^ (2 mL)	x			x	x				x^C^
Hepatitis B surface Ag (1 mL)	x								
DBS/Plasma PK Sample (3-5 mL)			x	x	x	x	x	x	x
Fingerstick (DBS) (0.1 mL)			x	x	x	x	x	x	x
Spot Urine Sample (5–10 mL)			x	x	x	x	x	x	x
Collection of 24-h Urine					x	x			
Oral Fluid			x	x	x	x^e^			
PBMC (10 mL)			x	x	x		x^d^	x	x
Store plasma/EDTA Cell Pellet (3 mL)	X								
Total Blood Vol. (mL)	10 mL	0 mL	15 mL	17 mL	39 mL	25 mL	20 mL	15 mL	32 mL

^a^Hematology: hemoglobin, hematocrit, RBC, MCV, WBC and differential, platelets

^b^Chemistry: AST, ALT, total bilirubin, BUN, creatinine; electrolytes: sodium, potassium, chloride, bicarbonate, calcium, phosphate

^c^Only at End of Week 10

^d^Only On Monday of Week 8

^e^Only on Wednesday, Thursday, Friday of Week 7

### Intensive 24-h PK blood sampling phase

On the Monday morning of Week 7, a pre-dose blood sample is drawn and a single Truvada® tablet is administered by the study team on an empty stomach (with at least 6 h fast beforehand). This is the last dose of Truvada® for all subjects. Venous blood samples are then collected at 1, 2, 4, 6, 8, 10, 12 and 24 h post-dose. At each time point, a venous blood dried blood spot (DBS, 5 spots) and fingerstick DBS (2 spots) are collected. Oral fluid samples are collected at pre-dose, 1, 4, 12 and 24 h post-dose. Urine samples are collected pre-dose and over the intervals of 0–4 h, 4–8 h, 8–12 h, and 12–24 h. PBMCs are only collected pre-dose. Renal and liver function tests are performed for safety evaluations.

### 4-week wash-out phase

After the intensive PK sampling is complete, subjects return to the clinic once a day for the remaining 5 days of Week 7 for blood, urine (24-h) and oral fluid specimen collection (Table 2).

Blood and urine are collected on Monday and Thursday of Week 8, and then on Monday morning of Weeks 9 and 10. Blood and urine are collected and a final blood chemistry is performed at the last study visit (end of Week 10) on the following Monday morning.

### Assessment of study treatment adherence

We are utilizing several monitoring tools to ensure strict compliance to the assigned randomized adherence groups. Directly Observed Therapy (DOT) is performed for each study drug intake for all subjects. Subjects are asked to come to the clinic each morning they are required to take the study treatment. At weekends (specifically for Groups 1 and 2), DOT is remotely implemented to document each drug administration, either via video call or mobile phone application. To complement DOT, each subject is also provided with an electronic “Wisepill” box (https://www.wisepill.com), whereby mobile phone and internet technologies send a message in real-time to a central database each time the subject opens the pill box. The study team closely monitors the records of the Wisepill box use and is able to cross reference results with the DOT records.

